### Monthly Monitoring

#### Physical Activity, Sedentary Behavior, and Sleep

Physical activity and sleep quality and quantity were measured using accelerometry (ActiGraph GTX3+, ActiGraph LLC, Pensacola, Florida), and sedentary behavior was measured using activPAL (activPAL3c, PAL Technologies Ltd, Glasgow, UK) at preintervention, week 4, week 8, and postintervention. The ActiGraph was initialized to record data in 60-second epochs and was set to measure motion in all 3 axes, with the inclinometer function activated. The ActiGraph was worn on the right hip with a lightweight belt, and participants were instructed to wear it for 24 hours a day over a 7-day period, except when swimming, bathing, and showering. Participants were instructed to complete a sleep diary to capture awake and sleep times. Physical activity and sleep data were captured and analyzed using the ActiLife Software Version 6 (ActiLife software; Pensacola, FL, USA). A minimum of 4 days of wear time, with 600 min per day of wake time was required for data analysis. The 4 days of wear needed to be inclusive of 3 weekdays and 1 weekend day. For the exercise group, at least one of the weekdays needed to be an “exercise day.” Nonwear time was defined as 60 continuous minutes of no counts (zeros) [54]. Vector magnitude cut-points were used for analysis [55,56]. The vector magnitude represents the summed value of all 3 axes measured from the ActiGraph, calculated as the square root of the total sum of each axis, squared (X^2^+Y^2^+Z^2^), then square rooted [57]. Counts/minute between 200 and 2689 represents light intensity physical activity, 2690 to 6166 represents moderate intensity physical activity, 6167 to 9642 represents hard intensity physical activity, and >9643 counts per minute represents very hard intensity physical activity. Data were analyzed for any physical activity occurring in 1-min and 10-min bouts/intervals. Within each 10-min bout, 1- or 2-min of “dropped” counts were allowed, thereby excluding bouts of activity where a drop-in count is greater than 2 min (within the 10-min period) occurred. Sleep data were analyzed for sleep latency, total sleep time, wake after sleep onset, and sleep efficiency. Participants completed a sleep diary that was used to mark wake and sleep hours, which was further verified based on movement measured by the activPAL.

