#### Dietary Intake

At the same time points as the physical activity data collection, dietary intake was estimated using a 24-hour recall and a 3-day dietary record, including 2 weekdays and 1 weekend day. In addition, a food frequency questionnaire was administered before and following the intervention. Nutrient intake and food group analysis were calculated using the South African Food Composition Database System (SAFOOD, the South African Food Composition Database, South African Medical Research Council, Cape Town, South Africa).

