### Statistics

#### Sample Size Determination

Sample size determination was based on our primary outcome using the study of Nordby et al [80], with a significance level of *P*<.05 and power of 80%. On the basis of the change in normalized glucose clearance (measured using a euglycemic hyperinsulinemic clamp) from pre- to postintervention (12-week aerobic training) compared with the nontrained control group (8.2 [SD 5.9] vs −1.8 [SD 6.2] mL/kg/min FFM/nmoL/L insulin, respectively), 6 participants per group would be required to detect a significant difference between groups. These numbers correspond to those of Ortega et al [81] who compared glucose tolerance tests to detect the insulin sensitizing effects of a bout of continuous exercise and reported that 6 participants would be required to detect a change in insulin sensitivity when using a FSIGT. In order to account for the secondary outcomes, using changes in skeletal muscle glucose transporter (GLUT)4 in response to a 12-week training program as the proxy (0.65 [SD 0.69] vs 0.01 [SD 0.69] AU for training vs control group), 18 women would be required to detect a difference between groups [81]. On the basis of these calculations, and a dropout rate of 10% (2/20), 20 participants per group were selected.

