#### Proposed Statistics

Results will be presented as means (SD), or medians and interquartile ranges for non-normally distributed data. Data will be normalized by log transformation if required. Repeated measures ANOVA will be used to compare differences in the change of outcome variables between the control and exercise groups in response to the exercise/control intervention. Pearson and/or Spearman correlations will be used to examine associations between changes in primary and secondary outcome variables. Data will be analyzed using StataSE (version 14, StatCorp, Texas, USA) and IBM SPSS Statistics 24 (Version 24.0, Armonk, NY, USA).

Comprehensive metabolite profiling data will be evaluated via a combination of multivariate analysis methods and univariate statistics, that is, Principal Component Analysis (PCA), Orthogonal Partial Least Squares (OPLS), and its extensions [64]. In addition, we will perform an extensive validation to determine the model significances, using both internal, ANOVA on the cross-validated model patterns, and external validation, independent sample prediction. Model scores (subject level) will be used to visualize and interpret the differences in metabolic response between predefined patient groups or subgroups, or of individual patients responding differently to the interventions. Model loadings (variable level) combined with univariate *P* values will be used as the base for mechanistic interpretation and to highlight significant metabolites or metabolite patterns.

For bacterial community analysis, basic statistical tests will be performed using QIIME [77] and R software will be used for advanced statistical analysis. Beta-diversity will be evaluated by calculation of weighted and unweighted Unifrac distances. The Shannon and Simpson diversity indices will be employed to study alpha-diversity. The relationship between the composition of the fecal bacteria and exposure variables will be determined using weighted generalized ridge regression methods [82] and the lasso [83]. We will use Dirichlet multinomial models or ecological approaches such as multi-species occupancy models to evaluate interactions and shift in fecal bacterial communities over time [84,85].

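### For the secondary outcomes measured at four windows, a wide-format repeated measures ANOVA would drop any completer with one invalid window; a mixed model on every valid window keeps her data

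*Protocol article*

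**What the plan says.** The Proposed Statistics section gives one general method for between-arm change: "Repeated measures ANOVA will be used to compare differences in the change of outcome variables between the control and exercise groups". On software it says "Data will be analyzed using StataSE (version 14, StatCorp, Texas, USA) and IBM SPSS Statistics 24", without saying which program fits the ANOVA.

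Activity, sleep and sedentary behavior are recorded "at preintervention, week 4, week 8, and postintervention" (Physical Activity, Sedentary Behavior, and Sleep). Diet follows the same schedule: "At the same time points as the physical activity data collection, dietary intake was estimated using a 24-hour recall and a 3-day dietary record" (Dietary Intake). Aims and Objectives lists all of these as secondary determinants.

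For the ActiGraph outcomes the article sets a wear rule: "A minimum of 4 days of wear time, with 600 min per day of wake time was required for data analysis", and "The 4 days of wear needed to be inclusive of 3 weekdays and 1 weekend day". In the exercise arm, one of the weekdays must also be a training day. No comparable rule is given for activPAL or diet.

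The article does not say whether all four windows or only the first and last enter the ANOVA, or what happens to a woman with one invalid window.

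**The concern.** A pre/post outcome and a four-window outcome behave differently under repeated measures ANOVA. With two visits, a woman who misses one has no observed change to contribute. With four visits, a woman who misses one still has three usable measurements, and the wide-format procedure discards them all. The ActiGraph rule makes scattered loss of single windows plausible even among women who finish the trial.

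These outcomes are secondary, but they carry weight in interpretation. The article uses accelerometry to verify that controls did not take up exercise, and its Discussion counts the four-weekly monitoring as a strength. A non-significant result from a needlessly reduced sample could be read as evidence that lifestyle stayed constant.

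**Working it through.** **The plan's own figures.** Sample Size Determination covers the primary outcome and a GLUT4 proxy only. For the primary outcome it uses "8.2 [SD 5.9] vs −1.8 [SD 6.2] mL/kg/min FFM/nmoL/L insulin, respectively": difference 10.0, pooled SD √[(5.9² + 6.2²)/2] = 6.05, so n = 2 × (1.96 + 0.84)² × 6.05²/10.0² ≈ 5.7, or 6 per group as stated. The GLUT4 proxy gives 19 per group by the same formula against 18 stated, and 18/0.9 = 20. No figure covers the four-window outcomes.

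**Inputs from the article.** Completers: 20 exercise + 15 control = 35. Baseline activPAL data (Table 2): 15 + 19 = 34 of 35 completers (97%), and 41 of 45 overall (91%). Baseline diet: 35 of 35 completers. No validity count is given for ActiGraph at any visit, or for any device after baseline.

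**Assumptions.** Validity v per window of 97%, 90% or 85%, with losses independent and unrelated to outcome; within-woman correlation 0.5 with compound symmetry; a between-arm difference of 0.7 SD at weeks 4, 8 and postintervention; two-sided 5%.

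**Step 1: women left by complete-case analysis.** Expected number = 35 × v⁴.
- v = 0.97: 31.0
- v = 0.90: 23.0
- v = 0.85: 18.3

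**Step 2: closed-form power of the 3-df test on N complete women, without sphericity correction.** λ = (20 × 15/35) × (N/35) × [0.7²/(1 − 0.5)] × 0.75. The 0.75 is the sum of squares of the pattern (0, 1, 1, 1) about its mean. At N = 35, λ = 8.571 × 0.98 × 0.75 = 6.30. Error df = 3(N − 2).

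| N | λ | Power |
|---|---|---|
| 35 | 6.30 | 52% |
| 31 | 5.58 | 47% |
| 23 | 4.14 | 35% |
| 18 | 3.24 | 27% |

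Simulated complete-case ANOVA with a Greenhouse-Geisser correction is slightly lower: 45%, 34% and 23% at the three validity rates.

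**Step 3: same 3-df test, same 0.7 SD effect, mixed model on every valid window (simulated).**

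| Validity | Complete-case ANOVA | Mixed model |
|---|---|---|
| 97% | about 44% | about 53% |
| 90% | about 31% | about 48% |

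Type I error was at or below 5%. The 53% should be read against Step 2: with no missing data at all, the uncorrected test has 52%. So at 97% validity about 5 points (52 − 47) is the most that retained windows can add; the rest of the 9-point gap reflects the sphericity correction and simulation error. At 90%, 48 − 35 = 13 of the 17 points survive the same comparison.

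**Step 4: a second simulation at a larger effect.** The effect was scaled so that a pre-to-post contrast has 80% power with 35 women: d = √(1.944 × 0.5) ≈ 0.99 SD. Neither test had a sphericity correction; 500 runs per cell.

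| Missing per window | Sustained: ANOVA vs mixed | Linear build-up: ANOVA vs mixed |
|---|---|---|
| 3% | 79% vs 81% | 65% vs 68% |
| 9% | 66% vs 80% | 47% vs 62% |
| 15% | 49% vs 76% | 38% vs 60% |

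The gain is 2 to 3 points at 3% missing, 14 to 15 at 9%, and 22 to 27 at 15%.

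**The case against.** The strongest objection is that the loss is conditional. The article does not say that all four windows enter. Its wording on change in response to the intervention also fits a pre/post analysis with 1 df, where 35 × v² gives 33, 28 or 25 women. Stata's long-format ANOVA can keep partly observed women. A journal article may also leave the choice of windows and the handling of invalid ones to an analysis plan. All of this stands, so a reader who infers that the plan certainly deletes women, or certainly runs a 3-df test, goes beyond the text. What remains is that the article fixes one method for outcomes of two different structures, and a better one is available in the same software.

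Three further readings are tempting and not supported.

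- *A mixed model cures the unfocused test.* It does not: with visit as a factor, the arm-by-visit interaction still has 3 df. Nor is the 3-df test always inferior. With full data and the 0.99 SD effect, it has 84% for a sustained difference, against 80% for pre-to-post.
- *The main contrast should be weeks 4 and 8 minus baseline.* At 97% validity this loses to the ANOVA for a gradual change (20% vs 33%) and has almost no power for a change seen only at the last window (5% vs 46%). For ActiGraph activity, the exercise arm's valid windows must include a training day. An arm difference at weeks 4 and 8 therefore contains the training itself and cannot show that nothing else changed.
- *Every four-window outcome is equally exposed.* The wear rule is stated only for ActiGraph. Baseline diet was complete and activPAL nearly so among completers.

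**Conclusion.** The point holds as a conditional, secondary-outcome matter. If all four windows enter a wide-format ANOVA, completers with one invalid window are lost. A mixed model on every valid window recovers most of that loss at no cost.

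The size depends on validity rates that the article does not report. At 97% per window the real gain is a few points of power. At 90% it is roughly 13 to 17 points for a sustained 0.7 SD difference. At 85% only about 18 of 35 women would remain. The 90% and 85% rates are assumptions, and the calculations also assume random loss of windows and compound symmetry.

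The gain is likely small for diet and sitting. A reader might infer that the primary result or the trial's dropout problem is involved, but neither is: insulin sensitivity and secretion are pre/post outcomes, and a mixed model learns little about change from the 10 dropouts if they have baseline data only.

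**What to change.** For the outcomes measured at four windows, replace repeated measures ANOVA with a linear mixed model (Stata mixed or SPSS MIXED): fixed effects for arm, visit and arm-by-visit, a random effect for woman, fitted to every valid window, with small-sample degrees of freedom. State that all four windows enter and that an invalid window is treated as missing without removing the woman.

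Keep the postintervention window in the main comparison. Weeks 4 and 8 minus baseline can be reported as a supplementary contrast, but not as the only main one. For ActiGraph activity, say that between-arm differences during the intervention include the training sessions. Report the number of valid windows by arm and visit, so that the actual loss can be seen.

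The cost is a change of analysis wording, with the same data and the same software. Study Design says that data analysis is already under way, so the change should be recorded before these particular outcomes are analysed.

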**Conclusions:**

The study describes a research protocol for an exercise intervention to understand the mechanisms underlying insulin sensitivity and secretion in obese black SA women and aims to identify causal pathways underlying the high prevalence of insulin resistance and risk for T2D in black SA women, targeting specific areas for therapeutic intervention.

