Overall, exercise training improves cardiorespiratory fitness and reduces cardiometabolic risk factors associated with the development of T2D. Accordingly, exercise training is consistently used as a model to examine putative mechanisms underlying insulin resistance and risk for T2D. To our knowledge, there are no studies that have examined the effect of exercise training on insulin resistance in obese black SA women who are at high risk for T2D. Therefore, the primary purpose of this research study is to gain a better understanding of the causal mechanisms underlying insulin resistance and risk for T2D in black SA women, using exercise as an intervention.

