### Aims and Objectives

The aim of the study was to identify mechanisms underlying the changes in insulin sensitivity and secretion in response to a 12-week aerobic exercise intervention in obese black SA women.

The objectives of the study were as follows:

to measure changes in insulin sensitivity and secretion (primary outcomes) in response to the 12-week intervention compared with the nonexercise control groupto measure changes in potential primary and secondary determinants (secondary outcomes) of insulin sensitivity and secretionto examine the associations between changes in insulin sensitivity and secretion and changes in the primary and secondary determinants

Primary determinants were as follows:

cardiorespiratory fitnessbody composition and body fat distributionblood pressurelipid profile, including high-density lipoprotein (HDL)- and low-density lipoprotein (LDL)-cholesterol subclasses and HDL functionalityectopic fat deposition (skeletal muscle, liver, and pancreas)skeletal muscle expression of genes and proteins involved in insulin signaling, oxidative capacity, and mitochondrial biogenesisskeletal muscle and serum metabolomics and lipidomic profilegluteal and abdominal subcutaneous adipose tissue expression of genes and proteins involved in inflammation, insulin signaling, oxidative stress, vascularization, adipogenesis, and lipid metabolismcirculating inflammatory cytokine, myokine, and adipokine concentrationsskeletal muscle and adipose tissue mitochondrial respiration and hydrogen peroxide production;gastrointestinal microbiota

Secondary determinants were as follows:

energy expenditure and substrate metabolism at rest and during exercisehabitual physical activity and sedentary behavior patternsdietary intake, red blood cell, and adipose tissue fatty acid compositionsleep quantity and qualitypsychological well-beingperceptions of body image, healthy behaviors, and the exercise intervention

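### The correlations of changes named for objective 3 carry no term for arm; if the arms are pooled, allocation itself produces associations between variables that both respond to training

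*Protocol article*

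**What the plan says.** The Protocol article sets a mechanistic purpose. The Introduction says the study is meant to "gain a better understanding of the causal mechanisms underlying insulin resistance and risk for T2D in black SA women, using exercise as an intervention", and the abstract's Conclusions say it "aims to identify causal pathways underlying the high prevalence of insulin resistance and risk for T2D in black SA women".

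Under Aims and Objectives, the third objective is to "examine the associations between changes in insulin sensitivity and secretion and changes in the primary and secondary determinants". The same section classes insulin sensitivity and secretion as primary outcomes and the determinants as secondary outcomes.

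Proposed Statistics then gives two general methods. For arm effects: "Repeated measures ANOVA will be used to compare differences in the change of outcome variables between the control and exercise groups". For associations: "Pearson and/or Spearman correlations will be used to examine associations between changes in primary and secondary outcome variables". Arm appears in the first sentence and not in the second. The second does not say whether the correlations are computed over all women or within an arm.

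**The concern.** A bivariate correlation over both arms mixes two things: whether women whose determinant changed more also had a larger change in insulin sensitivity, and whether both variables have different means in the two arms. Only the first bears on objective 3. The second is already covered by objectives 1 and 2. It appears in a pooled correlation whenever training shifts both variables, even if they are unrelated among women in the same arm.

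The trial is planned on the expectation that such shifts occur. Sample Size Determination assumes a training effect on insulin action and another on skeletal muscle GLUT4. The distortion would therefore fall mainly on the determinants expected to respond, which are the ones most likely to be put forward as mechanisms.

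**Working it through.** **Inputs**

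- Insulin action (Sample Size Determination): change 8.2 (SD 5.9) in trained and −1.8 (SD 6.2) in control participants. Difference 10.0; pooled SD = √((5.9² + 6.2²)/2) = 6.05; standardised effect 10.0/6.05 = 1.65. This is normalised glucose clearance from a clamp, used here as a proxy for the trial's FSIGT-based S_I.
- GLUT4 (same section): 0.65 against 0.01, SD 0.69; standardised effect 0.64/0.69 = 0.93.
- Completers (Results, Participant Enrollment, Allocation, Follow-Up, and Analyses): 20 exercise, 15 control.
- Assumed: two-sided 5% tests, and normally distributed changes with equal SDs in both arms.

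**The article's own figures first.** With n per group = 2(1.96 + 0.84)²(SD/difference)²:

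- insulin action: 5.7, so 6, as stated;
- GLUT4: 18.2, which rounds up to 19, against 18 stated (read as per group);
- 18/0.9 = 20 per group, as stated.

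These agree closely enough to use the effects as planning values.

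**Pooled correlation when the within-arm correlation is zero.** With v = (20/35)(15/35) = 0.245 and standardised effects d1 and d2,

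r = v·d1·d2 / √((1 + v·d1²)(1 + v·d2²)).

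For 1.65 and 0.93: 0.375 / √(1.669 × 1.211) = 0.26. Pearson's r is significant at N = 35 once |r| exceeds 0.33, so a true pooled value of 0.26 crosses that line often.

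**Rejection rates** (simulation, 40,000 trials per row, within-arm correlation exactly zero, nominal 5%; Monte Carlo standard error at most 0.25 percentage points):

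| Effects on the two variables (SD) | Population pooled r | Pooled Pearson | Adjusted for arm | Exercise arm only |
|---|---|---|---|---|
| 1.65 / 0 | 0.00 | 5.1% | 5.0% | 4.9% |
| 0.5 / 0.5 | 0.06 | 6.3% | 4.9% | 5.2% |
| 0.8 / 0.8 | 0.14 | 12.6% | 5.1% | 4.9% |
| 1.65 / 0.5 | 0.15 | 14.6% | 5.0% | 5.1% |
| 0.93 / 0.93 | 0.17 | 17.4% | 5.0% | 5.1% |
| 1.65 / 0.93 | 0.26 | 35.5% | 5.0% | 5.0% |
| 1.65 / 1.65 | 0.40 | 72.5% | 4.9% | 5.1% |

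Using Spearman instead does not help: 36.0% at 1.65/0.93.

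**Price of the alternatives.** By Fisher's z, the smallest |r| detectable with 80% power is tanh(2.80/√(N − 3)). For N = 35 this is 0.46; losing one further degree of freedom to arm, tanh(2.80/√31), still gives 0.46. For the 20 exercise women alone it is 0.59.

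**Number of tests.** Aims and Objectives lists 11 primary and 6 secondary determinant families. Against two outcomes that is at least 17 × 2 = 34 correlations, or 34 × 0.05 = 1.7 expected false positives if all nulls are true, separately from the arm problem.

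**The case against.** The strongest reply is that pooling is never stated. The article defines a training dose for the exercise group alone and mentions individual differences in response, so within-arm correlations are not excluded, and those keep the 5% level. This stands: the inflated rates apply to the pooled reading only. But the sentence allows pooling and pooling is its natural sense. The choice moves the error rate from 5% to about 35% at the planning effects, so it should be fixed in the text.

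A second reply is that a condensed article leaves covariates and multiplicity rules to a full analysis plan. For multiplicity that is fair, and the absence of a false discovery rate rule for these correlations does not carry the point. For arm, the article names a method for its third objective, and a better one is available on the same data.

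Third, simple correlation is not the only tool named. The article also lists OPLS with validation for metabolites, ridge regression and lasso for microbiota, partial least squares regression in the Discussion, and a q<.05 rule for the muscle gene array. A reader might infer that the plan has no error control or no other route to mechanism, and the document does not support that. Equally, none of these tools is said to adjust for arm or to replace the correlations.

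Finally, a reader might infer that the results will be reported as causal. Objective 3 and Proposed Statistics both speak of associations, the abstract states an aim, and the Discussion allows that secondary data may serve as pilot data. Causal reporting is a risk created by the stated aim; it is not something the plan commits to.

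**Conclusion.** The point holds in a limited form. The general method given for objective 3 has no arm term. If the arms are pooled, the chance of a spurious association between two variables that are unrelated within arm is about 35% at the article's planning effects, against a nominal 5%.

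It is tempting to say that any two variables that respond to training will look linked. The figures do not support that: the probability is raised, by little for modest effects (about 6% at 0.5/0.5 SD) and greatly only for large ones (about 72% at 1.65/1.65 SD, a size the article assumes for no determinant). There is no inflation if only one of the two responds.

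The size rests on the pooled reading, on 35 completers, on normal changes with equal SDs, and on a clamp-based effect as proxy for insulin sensitivity; the article gives no between-arm FSIGT effect. The between-arm comparisons of objectives 1 and 2 and the sample size are not affected.

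**What to change.** State in Proposed Statistics that the main association analysis is adjusted for randomised arm: either a partial correlation of the two changes given arm, or a regression of change in S_I (or secretion) on change in the determinant with arm as covariate. Keep unadjusted pooled correlations, if shown at all, as description. Word the results as associations and not as causal pathways, since both changes are measured after randomisation and adjusting for arm does not make their relation causal.

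Two additions are optional: baseline values as covariates (the simulation does not bear on these), and a false discovery rate rule over the determinant-by-outcome tests, of which there are at least 34.

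The change needs no new data. It costs about one degree of freedom per test, and fewer associations will reach significance. With N = 35 the analysis has 80% power only for |r| of about 0.46 or more. Restricting to the exercise arm would also hold the 5% level, but raises that threshold to about 0.59.
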